#### Record

We will record the outcomes in detail, including the onset time, diagnosis time, symptoms, adherence, and medicine cost. The incidence in each stage will be calculated and used to explore complex relationships among the outcomes.

### Data collection

Data will be collected at four stages: the perioperative stage, chemotherapy therapy stage, radiation therapy stage, and follow-up stage. Having completed the previous phase, we move on to the next. The total expenditure on healthcare will be computed for each treatment period. All authors could access information that could identify individual participants during data collection and statistical analysis.

#### First stage—perioperative stage

Data will be collected at the time of the perioperative stage, including demographic data (sex, age, race, ethnicity, marital status, socioeconomic status, educational status, and BMI), clinicopathological factors (pathological type, breast cancer location, TNM staging, and comorbidities), surgery information (date of diagnosis, date of surgery, type of surgery, type of surgical incision, lymph node management, the total number of dissected lymph nodes), and baseline information (upper-limb volume difference, scale results of Beck Depression Inventory-II). Patient information in the perioperative stage will be collected through the electronic medical record after obtaining written informed consent. We will manage to build a follow-up database preoperatively. We will use this follow-up database for baseline and data collection, transfer, and storage.

#### Secondary stage—chemotherapy therapy stage

Data will be collected at the time of the chemotherapy therapy stage, including the number of chemotherapy cycles, body mass index (BMI), upper limb volume measurement, assessment of tumor recurrence, and scale results of the Beck Depression Inventory-II. Once they receive the first round of chemotherapy, participants will be followed up in a regular oncology ward each cycle. Data collectors will conduct breast cancer-related lymphedema surveillance through upper-limb volume measurements. For patients who increase the upper-limb volume difference by more than 200 ml, secondary lymphedema is confirmed and diagnosed by a physician and physical therapist. Data will be collected at the time of the radiation therapy stage including the total number of radiation therapy cycles, body mass index (BMI), upper limb volume measurement, assessment of tumor recurrence, and scale results of the Beck Depression Inventory-II.

#### Third stage—radiation therapy stage

Radiation therapy cycles terminate at relatively short times. Therefore, data on the main factors will only be collected before radiation therapy cycles and after stopping the planned radiation treatment.

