**Perioperative stage**					
before surgery	√	/	/	√	√

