**Radiation therapy stage**					
before radiation therapy	√	√	√	√	√
after radiation therapy	√	√	√	√	√

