### Statistical analyses

The following primary factors will be calculated when each of the study stages (perioperative stage, chemotherapy therapy stage, radiation therapy stage, follow-up stage) is completed: BCRL incidence, RBC rate, and incidence of depression. To calculate the incidence of the primary outcomes, we will sum the total of participants within each of the stages as the denominator and sum the total of people with one of the primary outcomes as the numerator. For every statistical analysis, the participants will be classified into two groups based on whether they developed secondary lymphedema. Incidence rates of breast cancer recurrence and depression will be calculated separately for groups. The chi-square test will be used to compare the rates rate between the two groups [26]. As a secondary outcome, depression symptoms will be repeatedly measured in this study. The results of the assessment of depression symptoms will be compared across periods and between treatment-related events using statistical analysis with repeated measures analysis of variance (ANOVA).

We will identify clinicopathological factors, surgery information, lymph node management, breast cancer-related treatment, and body mass index(BMI) as risk factors due to their reported associations with secondary lymphedema, recurrence of breast cancer, and depression symptoms. Multivariate logistic regression will be used to determine whether secondary lymphedema and other parameters can predict breast cancer recurrence. To assess the correlates with these risk factors and outcomes, we will describe the strength of the association using clinically meaningful and statistically significant effect sizes, and a correction will be based on demographic characteristics.

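### The radiation stage's first visit precedes any radiation, and the counting rule lets outcomes found there enter radiation-stage incidence

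*Protocol article*

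**What the plan says.** The section on the third stage limits data collection in the radiation stage to two occasions: "data on the main factors will only be collected before radiation therapy cycles and after stopping the planned radiation treatment". Table 1 agrees. Its radiation therapy block has two rows, "before radiation therapy" and "after radiation therapy", and lymphedema, recurrence and the Beck inventory are ticked in both.

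The Record section makes stage incidence an output with a purpose: "The incidence in each stage will be calculated and used to explore complex relationships among the outcomes". Statistical analyses gives the rule: "we will sum the total of participants within each of the stages as the denominator". The numerator is the total of people with the outcome. The rule does not limit the numerator to new cases, does not limit the denominator to women still free of the outcome, and names no visit as a stage baseline.

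The Record section also says that onset time and diagnosis time will be recorded. The incidence rule does not use either.

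**The concern.** Data collection states that each stage begins once the previous one is complete. The pre-radiation visit therefore looks back over the interval since the last chemotherapy assessment, and nothing found there can have arisen during radiation. Table 1 nevertheless places it in the radiation stage as an outcome assessment, and the counting rule admits whatever is found.

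Two kinds of case enter the radiation-stage figure by this route: those first found at the pre-radiation visit, and those already known from the chemotherapy stage and still present. The first kind is also lost from the chemotherapy stage, where it arose or to which it is closest.

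What is at stake is the stage profile. The Discussion promises a whole-course account of incidence to inform a screening programme, and a profile that places events one stage late misleads on when screening would find them.

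**Working it through.** **The passages side by side**

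| Place | What it fixes |
|---|---|
| Table 1, row "before surgery" | lymphedema and recurrence marked with a slash: not assessed as outcomes |
| Table 1, row "before radiation therapy" | lymphedema and recurrence ticked, inside the radiation stage |
| Statistical analyses | numerator: all people with the outcome; denominator: all participants in the stage |

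The first row shows that the table has a way to mark a visit as not counting towards these outcomes. It was not used for the pre-radiation visit. Applied as written, the rule puts outcomes found at that visit into the radiation-stage numerator.

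**The plan's own figure**

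The protocol gives no stage-level rate to reproduce. Its sample size supplies the number of women. With N = z²p(1−p)/d², p = 0.1757, d = 0.02 and two-sided 5% (assumed, as it is not stated):

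- 1.96² × 0.1757 × 0.8243 / 0.0004 ≈ 1391
- 1391 / 0.9 ≈ 1546, within 1% of the stated 1557
- Evaluable women: 1557 × 0.9 ≈ 1401

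**Cases first found at the pre-radiation visit**

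Assumptions: constant hazard over three years (156 weeks), and a gap of 2 to 4 weeks between the last chemotherapy assessment and the pre-radiation visit. The protocol gives neither.

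- Lymphedema hazard: −ln(1 − 0.1757)/156 ≈ 0.00124 per week
- 2 weeks: 1 − exp(−2 × 0.00124) ≈ 0.25 percentage points; × 1401 ≈ 3 women
- 4 weeks: 1 − exp(−4 × 0.00124) ≈ 0.49 percentage points; × 1401 ≈ 7 women
- Recurrence at 15.53%: −ln(1 − 0.1553)/156 ≈ 0.00108 per week, giving about 0.2 to 0.4 percentage points

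As a share of first-found radiation-stage events, this is gap/(gap + course length). With an assumed course of 5 to 6.5 weeks it runs from 2/8.5 = 24% to 4/9 = 44%. With an assumed 3-week course it runs from 2/5 = 40% to 4/7 = 57%.

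**If earlier cases are counted too**

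Three-year lymphedema cases: 1401 × 0.1757 ≈ 246. Suppose a fraction f is present at the pre-radiation visit and a fraction g arises during radiation. The rate as written is 246(f + g)/1401. The rate of new cases among women at risk is 246g/(1401 − 246f).

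| f | g | As written | New, at risk | Ratio |
|---|---|---|---|---|
| 5% | 10% | 2.6% | 1.8% | 1.5 |
| 5% | 5% | 1.8% | 0.9% | 2.0 |
| 50% | 10% | 10.5% | 1.9% | 5.5 |
| 50% | 5% | 9.7% | 1.0% | 10.0 |

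The values of f and g are illustrative; the documents support no particular pair.

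**The case against.** **Collecting data before radiation is sound.** The sentence on the third stage describes only timing, and a measurement on each side of treatment is what a change analysis needs. This stands. The fault lies in joining the Table 1 allocation to the counting rule.

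**Stages are phases of care, not causal claims.** A reader might infer that the plan attributes these events to radiation as their cause. No section does so: treatment enters the association analysis as a risk factor. The point is limited to timing.

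**The size is small, or belongs elsewhere.** Cases first found in a short gap amount to a fraction of a percentage point, well inside the 2% permissible error. That stands, although the 2% was set for a three-year rate and a stage rate is itself small. The larger ratios come from counting earlier cases again, a feature of the rule that reaches other stages too. They show what the wording allows and should not be read as the effect of this one visit.

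**A boundary visit must fall somewhere.** The first chemotherapy cycle raises a similar question, and visit windows are often left to an analysis plan. Here, however, the protocol fixes both the stage of the visit and the numerator and denominator, so the objection is to what is stated.

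**Depression scores.** A reader might infer that the pre-radiation Beck score is averaged into the radiation period, so that a change during radiotherapy is diluted. The text does not support this. It says only "The results of the assessment of depression symptoms will be compared across periods and between treatment-related events", using repeated measures ANOVA. No section averages the two visits or defines a period as a stage mean, and the wording is compatible with treating them as separate time points.

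**Conclusion.** The point holds for stage-specific incidence of lymphedema and recurrence. Followed as written, the plan counts outcomes found before any radiation as radiation-stage outcomes.

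Its size cannot be derived from the documents. For lymphedema first found at the pre-radiation visit, about 0.25 to 0.5 percentage points is a reasonable illustration, resting on the assumed gap and a constant hazard. A hazard higher during treatment than later would raise it roughly in proportion. The 24% to 57% shares rest on assumed course lengths as well, and are shares of a small count. Counting earlier cases again would add more, by an amount that the documents do not fix.

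The three-year cumulative incidence, which is the primary time frame, and the sample size of 1557 do not change. This is a modest correction to a secondary presentation of the results, worth making because it is almost free.

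**What to change.** In Table 1, treat the pre-radiation visit as the end of the chemotherapy stage and as the baseline of the radiation stage. In Statistical analyses, define radiation-stage incidence as follows:

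- numerator: women whose event is first found at the post-radiation visit
- denominator: women in the stage who were free of that event at the pre-radiation visit

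Use the recorded onset and diagnosis times to place events that fall between visits. Events first found at the pre-radiation visit then count in the chemotherapy stage. The same restriction to women still free of the event could be worded to cover every stage, which would also stop earlier cases being counted again elsewhere.

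The cost is one relabelled table row and one or two sentences. No visit, measurement or recruitment target changes.

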#### Last stage—follow-up stage

The follow-up stage is also the last stage of our cohort study. After finishing radiation and chemotherapy treatment, patients will be followed until 3 years after breast cancer surgery. Postoperative breast cancer patients are exposed to a chance of recurrence. The implementation of guideline-recommended follow-up plans for breast cancer patients is necessary. The patients in our study will be seen for follow-up visits once every three months [24]. Data will be collected at the time of the follow-up stage including BMI, upper limb volume measurement, assessment of tumor recurrence, and scale results of the Beck Depression Inventory II. Detailed cohort protocols in the four research stages are presented in Table 2.

**Table 2 pone.0285772.t002:** Detailed cohort protocols in four research stages.

**Perioperative stage**	
Demographic data	gender, age, race, ethnicity, marital status, socioeconomic status, educational status and body mass index (BMI)
Clinicopathological factors	pathological type, breast cancer location, TNM staging and comorbidities
Surgery information	date of diagnosis, date of surgery, type of surgery, type of surgical incision, Lymph node management, the total number of dissected lymph nodes
Baseline information	arm circumferences, scale results of Beck Depression Inventory-II
Financial information	treatment related cost
**Chemotherapy therapy stage**	
Time points information	the number of chemotherapy cycles
Main information	body mass index(BMI), arm volume measurement (secondary lymphedema), assessment of tumor recurrence, scale results of Beck Depression Inventory-II
Financial information	treatment related cost
**Radiation therapy stage**	
Time points information	total number of radiation therapy cycles
Main information	body mass index (BMI), arm volume measurement (secondary lymphedema), assessment of tumor recurrence, scale results of Beck Depression Inventory-II
Financial information	treatment related cost
**Follow-up stage**	
Time points information	the number of follow-up cycles
Main information	body mass index (BMI), arm volume measurement (secondary lymphedema), assessment of tumor recurrence, scale results of Beck Depression Inventory-II
Financial information	treatment related cost

### Quality assurance

To ensure the uniformity of data, all the nurses in our study will undergo unified training about the measurement of arm volume and how to provide guidance when patients complete the questionnaire. Arm volume will be measured twice, in the morning and at night, and the average of two measurements will be used in the analyses to minimize errors. All oncologists will receive unified training, including magnetic resonance imaging (MRI) analysis and diagnosis of breast cancer recurrence. Moreover, loss to follow-up will continue to hinder the data completeness of our cohort study. Therefore, the computer and application are programmed to alert patients by telephone and message before one day when breast cancer patients need to complete the follow-up.

### Sample size calculation

Sample size will be estimated using the sample size estimation formula for prevalence studies. ($N=\frac{\mu_{\frac{\alpha }{2}}^{2}(1‐p)p}{d^{2}}$) [24, 25]. The formally required sample size calculation was based on the actual incidence of the primary outcomes in the electronic medical record system of West China Hospital. The maximum permissible error is 2%. Based on retrospective data from the electronic medical record system from 2017 to 2020 in West China Hospital, we found a 3-year BCRL incidence rate of 17.57% after breast surgery or breast reconstruction in patients with breast cancer. The rate of BCR occurrence was 15.53% at three years. Assuming a 10% dropout rate, at least 1557 participants should be recruited in our cohort study. We are trying to recruit more breast cancer patients, considering the longevity of the study.

### Statistical analyses

The following primary factors will be calculated when each of the study stages (perioperative stage, chemotherapy therapy stage, radiation therapy stage, follow-up stage) is completed: BCRL incidence, RBC rate, and incidence of depression. To calculate the incidence of the primary outcomes, we will sum the total of participants within each of the stages as the denominator and sum the total of people with one of the primary outcomes as the numerator. For every statistical analysis, the participants will be classified into two groups based on whether they developed secondary lymphedema. Incidence rates of breast cancer recurrence and depression will be calculated separately for groups. The chi-square test will be used to compare the rates rate between the two groups [26]. As a secondary outcome, depression symptoms will be repeatedly measured in this study. The results of the assessment of depression symptoms will be compared across periods and between treatment-related events using statistical analysis with repeated measures analysis of variance (ANOVA).

We will identify clinicopathological factors, surgery information, lymph node management, breast cancer-related treatment, and body mass index(BMI) as risk factors due to their reported associations with secondary lymphedema, recurrence of breast cancer, and depression symptoms. Multivariate logistic regression will be used to determine whether secondary lymphedema and other parameters can predict breast cancer recurrence. To assess the correlates with these risk factors and outcomes, we will describe the strength of the association using clinically meaningful and statistically significant effect sizes, and a correction will be based on demographic characteristics.

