## Patients and methods

This study is a prospective cohort study of breast cancer survivors. This study aimed to investigate and evaluate the incidence and correlation of BCRL, BCR, and depression. The primary outcome measures include the incidence and correlation of BCRL and BCR within three years. Choice of the time frame because three years is a high-incidence period of BCRL and BCR. The secondary outcome is depression.

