Among patients with breast cancer treated, we found that being diagnosed with breast cancer-related lymphedema is associated with a modestly increased risk of breast cancer recurrence [27]. Breast cancer-related lymphedema dramatically impacts the quality of life. Secondary lymphedema, a primary complication, causes the most disability in breast cancer survivors [28]. Cancer recurrence threatens patients’ lives. Cancer recurrence drives the most deaths from breast cancer. According to evidence-based data, the presence of new-onset lymphedema should be confirmed to determine whether breast cancer first recurs. Moreover, conservative management is becoming the treatment of choice for secondary lymphedema. However, complete decongestive therapy (the first choice of conservative management) will not be used if the neoplasm is the cause of breast cancer-related lymphedema. Early screening and identification of secondary lymphedema and recurrence of breast cancer are of enormous significance to breast cancer medical prognosis. However, there is no continuous assessment longitudinal cohort established in China. We will focus on the correlation assessment between secondary lymphedema and breast cancer recurrence. This work will be the cornerstone of a well-directed screening program and help to develop a well-defined intervention. In the era of heightened whole-course management, serious complication screening and recurrence identification of breast cancer survivors may be even more important.

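### Recurrence is compared between women who ever and never developed lymphedema, with no rule on which came first, so lymphedema that follows recurrence counts as predicting it

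*Protocol article*

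**What the plan says.** The association is a primary outcome. Under Patients and methods: "The primary outcome measures include the incidence and correlation of BCRL and BCR within three years".

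The Statistical analyses section fixes how it is tested:

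- Grouping: "For every statistical analysis, the participants will be classified into two groups based on whether they developed secondary lymphedema".
- Outcome by group: "Incidence rates of breast cancer recurrence and depression will be calculated separately for groups".
- Unadjusted test: "The chi-square test will be used to compare the rates rate between the two groups".
- Adjusted model: "Multivariate logistic regression will be used to determine whether secondary lymphedema and other parameters can predict breast cancer recurrence".

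No ordering, landmark, person-time or censoring rule accompanies these statements. Two other places bear on the point. The Introduction says that recurrence may adversely affect lymphedema, and the Discussion says that one treatment is not used "if the neoplasm is the cause of breast cancer-related lymphedema". The Record section shows that timing will be available: "We will record the outcomes in detail, including the onset time, diagnosis time, symptoms, adherence, and medicine cost".

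**The concern.** Lymphedema is not a baseline characteristic. It can start at any time in the three years over which recurrence is also counted. Table 1 of the protocol article schedules both assessments at each chemotherapy cycle, around radiotherapy and every three months to year 3, so either can come first. An ever/never grouping treats a status reached late as though it had been known from surgery.

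The Discussion asks whether women with lymphedema have a higher risk of recurrence and whether screening for lymphedema could help find recurrence early. Both questions need lymphedema to come first. If recurrence brings on lymphedema, as the article allows, the planned analysis can give a clear positive association when lymphedema carries no risk and gives no warning. That result would then inform a screening programme.

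**Working it through.** **Inputs from the protocol article (Sample size calculation).** Three-year lymphedema incidence: "we found a 3-year BCRL incidence rate of 17.57% after breast surgery or breast reconstruction in patients with breast cancer". Three-year recurrence 15.53%; permissible error 2%; dropout 10%; 1557 to recruit.

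**The plan's own figure.** With two-sided 5% assumed, N = 1.96² × 0.1757 × 0.8243 / 0.02² = 1391, and 1391 / 0.9 = 1546. That is close to 1557 but not exact. The number rests on the precision of one proportion, so the present point leaves it unchanged. Evaluable women: 1557 × 0.9 = 1401.

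**Set-up (assumptions).** Constant hazards, and no effect of lymphedema on recurrence.

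- Lymphedema: hL = −ln(0.8243)/3 = 0.0644 per year.
- Recurrence: hR = −ln(0.8447)/3 = 0.0563 per year.

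**Step 1: how often the order matters.** Under independence, 1401 × 0.1757 × 0.1553 = 38 women have both events. The probability that recurrence comes first and lymphedema follows within three years is

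hR/(hR+hL) × (1 − 0.8447 × 0.8243) − 0.8243 × 0.1553 = 0.1416 − 0.1280 = 0.0136,

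or 19 of 1401. The other 19 have lymphedema first. About half of the women with both events are therefore in the wrong order for the question asked.

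**Step 2: the planned odds ratio.** The cells unaffected by what happens after recurrence are:

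- neither event: 0.8447 × 0.8243 = 0.6963
- lymphedema only: 0.1757 × 0.8447 = 0.1484
- lymphedema, then recurrence: 0.0273 − 0.0136 = 0.0137

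The remaining 0.1416 have recurrence first. They split into those who later develop lymphedema and those who do not, according to the multiplier k that recurrence applies to the lymphedema hazard. The odds ratio is (0.0137 + recurrence then lymphedema) × 0.6963 / (0.1484 × recurrence without lymphedema).

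| Assumed k | Recurrence then lymphedema | Recurrence without lymphedema | Odds ratio | Approx. chance of a false significant result, 1401 women |
|---|---|---|---|---|
| 1 (no reverse effect) | 0.0136 | 0.1280 | 1.00 | nominal |
| 1.5 | 0.0197 | 0.1219 | 1.29 | 30% |
| 2 | 0.0255 | 0.1161 | 1.58 | 75% |
| 3 | 0.0360 | 0.1056 | 2.21 | over 99% |

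A simulation of 4,000,000 women gave 1.00, 1.29, 1.59 and 2.20 for the same rows. Lowering the lymphedema hazard so that total incidence stays near 17.6% gave 1.58 at k = 2 and 2.19 at k = 3.

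**Step 3: if arm measurement stopped at recurrence.** All 0.1416 then fall in the no-lymphedema group: 0.0137 × 0.6963 / (0.1484 × 0.1416) = 0.45 (recurrence 8.5% against 16.9%). Exactly the same table arises if measurement continues but only lymphedema before recurrence is counted as exposure.

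**Step 4: lymphedema as a time-dependent exposure.** In the same simulations, each woman was counted as unexposed until lymphedema onset and followed to recurrence. The rate ratio lay between 0.995 and 1.006 in every scenario.

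**The case against.** The strongest reply is that the article promises a correlation, calls the study explorative, and schedules both assessments to year 3 whatever happens. With full observation and no reverse effect the planned odds ratio is exactly 1.00. The multipliers are not in the documents, recurrence includes local and distant disease, and nothing shows that it triples the arm-lymphedema hazard overall. Lymphedema caused by a tumour not yet detected is also useful signal for a screening aim.

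Much of this stands. The documents support the direction of the reverse effect but not its size. Useful signal, however, is lymphedema seen before recurrence is diagnosed, and the planned grouping does not separate it from lymphedema seen afterwards. Nor is the choice merely left to an unseen analysis plan: the article names the grouping for every analysis and names the tests.

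A reader might also infer that the comparison is certainly distorted downward by immortal time. The documents do not support that. The 0.45 needs arm measurement to end at recurrence, and Table 1 shows no such exit. Unequal follow-up is likewise a small matter: 10% random dropout gives 1.05, and an assumed 24-month uniform accrual within a 36-month window gives 1.09, whereas the article describes follow-up to three years after surgery.

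**Conclusion.** The concern holds for the order of events. As written, the primary association cannot separate lymphedema that precedes recurrence from lymphedema that follows it, although the article itself allows for the latter. With no true effect the odds ratio runs from 1.00 to about 2.2 for assumed multipliers of 1 to 3, under constant hazards and the article's three-year rates. The downward case of about 0.45 is conditional and is not a stated feature of the plan. Because the two mechanisms push in opposite directions, neither the sign nor the size of the planned estimate could be interpreted with confidence. This should be corrected before analysis.

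**What to change.** Make the main analysis a cause-specific Cox model for time from surgery to first recurrence:

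- lymphedema is a time-dependent covariate that switches on at its recorded onset;
- follow-up ends at recurrence, with censoring at the last visit and death treated as a competing event;
- lymphedema first recorded at or after recurrence is not exposure;
- adjustment uses the factors already listed for the logistic model.

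Do not keep the chi-square or logistic analysis and simply recode exposure as lymphedema before recurrence, for the reason shown in Step 3.

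A landmark comparison among recurrence-free women can be added as a secondary, descriptive analysis. It is too thin to be the main one. At 12 months, 1401 × 0.8447^(1/3) = 1324 women are recurrence-free, 6.24% of them (83) have lymphedema, and 10.64% of those (about 9) recur by 36 months. An exposure lag of one three-month visit should be a sensitivity analysis only, since it removes recurrences found through the lymphedema work-up, which matter for the screening aim.

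The cost is revised wording and some programming. The onset and diagnosis dates are already to be collected, and the stated sample size does not change. Precision will be modest: under no effect, about 19 recurrences follow lymphedema among 1401 women.

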#### Diagnosis standards

Diagnosis of BCRL: We used a 200 ml limb volume difference as the diagnostic standard. The 200 ml limb volume difference standard is a universal criterion recommended by the 2020 Consensus Document of the International Society of Lymphology [2]. The limb volume difference will be measured with a Perometer device(an automated optoelectronic measurement of arm circumferences) [17].

Diagnosis of RBC: Physical examination and magnetic resonance imaging (MRI) for screening surveillance of breast cancer survivors. Breast cancer survivors who had biopsy-proven recurrence of breast cancer at presentation documented by fine-needle aspiration biopsy or core needle biopsy [18–21].

Diagnosis of depression: The screening tool will be the Beck Depression Inventory-II. We used the Beck Depression Inventory-II rubric; The scores are subdivided into the following grades: minimal(0–13 points), mild(14–19 points), moderate(20–28 points), and severe (greater than 29 points) [22, 23].

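### For depression, the one test explicitly tied to the two lymphedema groups is an unadjusted chi-square on a yes/no rate; the plan should name a baseline-adjusted analysis of the BDI-II score

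*Protocol article*

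**What the plan says.** Four statements in the protocol article bear on this.

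- **Grouping** (Statistical analyses): "For every statistical analysis, the participants will be classified into two groups based on whether they developed secondary lymphedema".
- **Comparison of the groups** (same section): "Incidence rates of breast cancer recurrence and depression will be calculated separately for groups". The next sentence names the test: "The chi-square test will be used to compare the rates rate between the two groups".
- **Second analysis of depression** (same section): "The results of the assessment of depression symptoms will be compared across periods and between treatment-related events", using repeated measures ANOVA. This sentence does not mention the lymphedema groups and does not say whether the score or the grade is analysed.
- **Measurement** (Diagnosis standards): the instrument is the BDI-II. "The scores are subdivided into the following grades: minimal(0–13 points), mild(14–19 points), moderate(20–28 points), and severe" above that. No cut is named for counting a woman as depressed. Table 1 schedules the BDI-II at the "before surgery" time point and at every later visit, and the perioperative-stage section lists it as baseline information.

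Recurrence is treated differently. Besides the chi-square, it has a multivariate logistic regression with lymphedema as a predictor. No such model is named for depression. The only general adjustment mentioned is for demographic characteristics.

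**The concern.** The Introduction names the correlation between recurrence, lymphedema and depressive symptoms as an evidence gap, and Patients and methods makes depression the secondary outcome. The test explicitly attached to the lymphedema contrast uses only which side of a cut each woman falls on. It discards all variation on either side of the cut and takes no account of how depressed she was before surgery.

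Two things are at stake. First, only about 18% of women are expected to develop lymphedema, so the comparison is unbalanced, and cutting the score makes a modest real difference more likely to be reported as none. Second, the groups are not randomised and form after surgery. If women who later develop lymphedema were already more or less depressed beforehand, that difference passes straight into the crude comparison.

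**Working it through.** **The plan's own figure.** The Sample size calculation section uses N = z²p(1−p)/d² with p = 0.1757 and d = 0.02. This gives 1.96² × 0.1757 × 0.8243 / 0.0004 = 1391. Dividing by 0.9 for 10% dropout gives 1546, within 1% of the stated 1557. The article states no power for depression.

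**Inputs from the article.** Evaluable women: 1557 × 0.9 = 1401. Lymphedema at 17.57%: 246, leaving 1155 without. The only depression figure is in the Introduction, up to 30% of survivors with depressive symptoms.

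**Inputs assumed.** Two-sided alpha 0.05; one score per woman; a normal score with a true shift of d SD between groups; a depressed rate p0 without lymphedema of 10% to 30%; a correlation r of 0.3 or 0.5 between pre-surgery and later score.

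**Formulas.**
- Score: z = d / √[(1−r²)(1/246 + 1/1155)], with r = 0 if unadjusted. Power ≈ Φ(z − 1.96). Here √(1/246 + 1/1155) = 0.0702.
- Cut score: p1 = 1 − Φ(Φ⁻¹(1−p0) − d). Power ≈ Φ([p1 − p0 − 1.96·s0]/s1), where s0 is the pooled and s1 the unpooled standard error.

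**Worked case, d = 0.20 and p0 = 30%.**
- Cut: p1 = 37.3%, s0 = 0.0326, s1 = 0.0337. Power = Φ([0.0728 − 0.0638]/0.0337) = Φ(0.27) = 60.6%.
- Score, unadjusted: z = 0.20/0.0702 = 2.85. Power = Φ(0.89) = 81.3%. The loss from the cut is 20.7 points.
- Score, adjusted: about 85% with r = 0.3 and 90.8% with r = 0.5.

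**Range (power, %).**

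| Shift (SD) | Score | Score, r = 0.5 | Chi-square, p0 30% | p0 20% | p0 15% | p0 10% |
|---|---|---|---|---|---|---|
| 0.10 | 29.6 | 37.6 | 20.0 | 18.3 | 17.0 | 15.1 |
| 0.15 | 57.0 | 69.4 | 38.7 | 35.3 | 32.4 | 28.3 |
| 0.20 | 81.3 | 90.8 | 60.6 | 55.8 | 51.6 | 45.3 |
| 0.25 | 94.5 | 98.4 | 79.5 | 74.8 | 70.4 | 63.2 |
| 0.30 | 99.0 | 99.9 | 91.6 | 88.3 | 84.9 | 78.6 |

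The loss from the cut alone is smallest at 0.30 SD and 30% depressed (99.0 − 91.6 = 7.4 points) and largest at 0.20 SD and 10% depressed (81.3 − 45.3 = 36.0 points).

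**Skewed scores, by simulation with an assumed cut at 14.** With a gamma score of mean 10 and SD 9 moved by 0.20 SD, power is 44% for chi-square and 81% for the t-test. With a gamma score of shape 1.5, scaled so that 30% score 14 or more, and group means 15% or 20% apart, chi-square has 49% or 72%, the t-test 65% or 87%, and the rank test 59% or 81%. The size of the loss depends on the shape of the difference; its direction does not change in these cases.

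**The case against.** The strongest reply starts from the grouping sentence, which covers every statistical analysis. Read with it, lymphedema status is also a grouping in the repeated measures ANOVA, with the pre-surgery visit as one of its periods. The chi-square then serves the separate secondary objective of incidence, for which a rate is the right quantity, and the study loses no power on the score. The reply adds that the effect size, SD, distribution and cut are not in the article; that incidence is to be calculated at each stage, whereas the calculation uses one score and the three-year split; and that depression is secondary, the study calls itself exploratory, and the sample size was set for precision.

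Much of this stands. A reader might infer that the chi-square is the only comparison of depression by lymphedema in the plan. The documents do not support that, because the grouping sentence may bring the ANOVA in. A reader might also take 20 points as the power this study will lose. It is one case among those tried, and not a property of the plan. Nor do the documents support dropping the rates.

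The reply does not settle the matter. The ANOVA sentence names its own contrasts, and lymphedema groups are not among them. If the grouping does apply, the plan has two analyses of one question and does not say which one answers it. Even then the pre-surgery score is at most one more period: a group effect averaged over periods would include a value taken before lymphedema could occur, without adjusting for it. This is also not just detail left to an analysis plan, since the article itself fixes the crude test for these groups.

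**Conclusion.** The point holds in a limited form. For depression, the only test explicitly tied to the two lymphedema groups is an unadjusted chi-square on a yes/no rate. Whether the ANOVA also compares these groups is unclear.

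If the chi-square carries the comparison, the cut alone costs about 7 to 36 points of power over shifts of 0.10–0.30 SD and depressed rates of 10–30%. This rests on a normal score, one score per woman, the three-year split of 246 and 1155, and a cut that matches the assumed rate. If the ANOVA of the score carries it, that power loss does not arise. On either reading, pre-surgery depression is not adjusted for in groups that were not randomised.

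This should be changed, but it does not threaten the study: depression is a secondary outcome and the sample size does not rest on this test.

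**What to change.** Add one sentence to the Statistical analyses section. The association of lymphedema with depressive symptoms will be assessed on the post-surgery BDI-II score, by linear regression or a mixed model over the scheduled visits, with lymphedema status as a factor and adjustment for the pre-surgery BDI-II score, reporting the mean difference with its 95% CI.

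Keep the depression rates by group and their chi-square test for the incidence objective.

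No new data, visits or participants are needed, since every score is already scheduled. The downside is small. A mean score difference is less familiar to clinicians than a rate, which keeping the rates alongside it addresses. The score is likely to be skewed, so robust standard errors or a rank-based check should go with the model.
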